## Data analysis plan

### Sample size calculation

As the study objectives are largely descriptive, no sample size calculation is necessary. Instead, we selected our sample size such that the study is feasible and large enough to conduct comprehensive analyses. Therefore, our sample size is based on a national average of 30 childhood cardiac transplants per year,^24^ and a 60% recruitment rate. All eligible patients listed on the NHSBT register will be approached for consent, recognising that not all of these patients will receive a transplant during the lifetime of this study. However, any pretransplant blood samples that have been obtained are equally important to achieve the study’s primary outcome measure.

### Statistical analysis

Data from spectral flow cytometry will be analysed using the OMIQ platform (https://www.omiq.ai/). Automated clustering and dimensionality reduction will be used to identify immune cell populations by FlowSOM and Uniform Manifold Approximation and Projection, respectively. These techniques overcome the practical challenges associated with manual gating and user bias when analysing datasets from large flow panels.

Statistically different immune signatures between patients with early thymectomy and late or non-thymectomy, EBV+ and EBV− serostatus and between time points, will be identified by linear and generalised linear mixed models (statistical significance defined as p<0.05). Continuous variables will be assessed by Pearson correlation using the single linkage method to group patients by expression values, and non-continuous variables by non-parametric Spearman correlation, as appropriate. Viral loads will be serially quantified at each study time point to correlate changes in immune responses with the volume of circulating virus-infected cells. Tetrameric frequencies for population groups (eg, early vs late/non-thymectomy) will be compared using Mann-Whitney U test and between time points for paired patient sample using Wilcoxon signed-rank test.

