**Methods and analysis:**

Prospective and sequential immune monitoring will be performed for 34 heart transplant recipients and 6 renal transplant patients (aged 0–18 years), stratified into early (<1 year), late (>1 year) and non-thymectomy groups. Peripheral blood samples and clinical data will be taken before transplant and at 3, 6, 12 and 24 months post-transplant. Single cell analysis of circulating immune cells and enumeration of EBV-specific T-lymphocytes will be performed using high-dimensional spectral flow cytometry with peptide-Major Histocompatibilty Complex (pMHC) I/II tetramer assay, respectively. The functional status of EBV-specific T-lymphocytes, along with EBV antibodies and viral load will be monitored at each of the predefined study time points.

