## Introduction

Post-transplant lymphoproliferative disease (PTLD) is the most common childhood cancer in paediatric recipients of a solid organ transplant. This heterogeneous group of life-threatening lymphoid malignancies is typically driven by Epstein-Barr virus (EBV) infection.^1^ PTLD comprises a histological spectrum that ranges from indolent non-destructive B-cell lymphoid infiltrates through to more aggressive and destructive polyclonal or monoclonal B-cell lymphomas, for example, Burkitt lymphoma and diffuse large B-cell lymphoma. These destructive PTLD subtypes are indistinguishable from high-grade mature B-cell lymphomas seen in immunocompetent children.^2^ Their incidence is allograft-dependent and ranges from 1%–2% in renal transplant recipients to as high as 10%–15% in heart transplant patients.^1 3^

PTLD has one of the worst clinical outcomes among childhood lymphomas. The estimated 2-year event-free survival (EFS) is 70% compared with 94% in sporadic cases within the general paediatric population.^4–6^ In even starker contrast is the survival outcome for paediatric heart transplant patients, who ostensibly have an inferior EFS compared with other non-cardiac organ transplants.^7 8^ The reasons for this potential disparity are still poorly understood, although partly ascribed to a higher incidence of therapeutic complications from organ rejection and treatment-related toxicities.^9^

The pathogenesis of PTLD is complex and multifactorial. It involves the interplay between EBV-driven lymphoproliferation, iatrogenic immunosuppression and the suspected functional exhaustion of T-lymphocytes due to graft-initiated chronic antigen stimulation.^10^ The role of EBV is clearly established in children, many of whom experience primary infection from an EBV-mismatched organ.^1 3 4^ In vitro and in vivo studies focused mainly on adult monomorphic PTLD have demonstrated distinct patterns of viral protein expression in infected B-lymphocytes.^10 11^ These expression patterns likely influence both the cellular composition of the tumour immune microenvironment and aberrant immune signalling, which result in immune escape of tumour cells.^10^

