In paediatric heart transplant patients, cardiac surgery via median sternotomy in early childhood often requires routine thymectomy in order to access the heart and great vessels. Our earlier study retrospectively examined risk factors for PTLD in the largest UK cohort of paediatric orthotopic heart transplant patients to date.^3^ The risk of PTLD was found to be significantly higher in children with congenital heart disease (CHD) (HR=3.2; 95% CI=1.4 to 7.4) and early thymectomy in infancy (HR=2.7; 95% CI=1.3 to 5.2).^3^ Furthermore, children with CHD had persistently lower T-lymphocyte counts compared with children transplanted for acquired cardiomyopathy (CD4+: 430 cell/μL vs 963 cells/μL, p<0.01 and CD8+: 367 cells/μL vs 765 cells/μL, p<0.01).^3^ Similar studies have identified marked phenotypic and functional disruptions to the T-lymphocyte compartment in paediatric heart transplant patients compared with children receiving a liver or kidney transplant.^12 13^

During the first year of life, the thymus plays a crucial role in the development of cell-mediated immunity, providing a microenvironment for precursor T-lymphocytes to proliferate and differentiate into mature (naïve) T-lymphocytes.^14^ While it has been shown that neonatal thymectomy alone is associated with premature immunosenescence and an increased risk of viral infections such as Cytomegalovirus (CMV),^14^ little is known about the immunological consequences of early thymectomy in immunosuppressed transplant patients. In particular, there are no data on the synergetic impact of thymectomy and transplant-related immunosuppression on EBV-specific immunity and the subsequent risk of developing PTLD.

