## Methods and analysis

### Study design and setting

The Immunology of THymectomy And Childhood CArdiac transplant (ITHACA) study is a prospective nationwide cohort study recruiting children (0–18 years) from the two UK centres currently commissioned to provide paediatric heart transplant services: The Freeman Hospital, Newcastle upon Tyne and Great Ormond Street Hospital for Children, London. The study cohort will consist of 34 prospective heart transplant recipients and a non-thymectomy age-matched control group made up of 6 renal transplant recipients. All patients meeting the study’s eligibility criteria will be identified and recruited through their local transplant teams at the time of listing for cardiac or renal transplantation. The study opened to patient recruitment in March 2022 and is expected to recruit until June 2024.

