#### Immunophenotyping of circulating immune cell subsets

Circulating immune cell populations will be analysed in Newcastle University laboratories. Mononuclear cells (MNCs) will be isolated and cryopreserved from blood samples taken at each study time point. In addition, biobanked MNC samples from age-matched healthy children will be included for analysis as non-thymectomy, non-transplant controls. Circulating immune cell subsets will be identified within samples using high-dimensional spectral flow cytometry (Aurora system (Cytek)). The 5-laser Aurora spectral cytometer enables an in-depth analysis of up to 40 cell surface markers at a time.^16^ This is highly valuable in phenotypically characterising various immune cell populations and their subsets (including T-lymphocytes, B-lymphocytes, Natural Killer [NK] cells and dendritic cells) in low volume paediatric samples.^17^ These samples will be analysed simultaneously in batches to mitigate interassay variation. A comprehensive list of cell surface markers has been selected to comprise the following:

Major innate/adaptive cell lineages.Main T-lymphocyte subsets as well as putative T-helper subsets.Recent thymic activity.Cellular exhaustion and senescence.Key innate/adaptive cells involved in immune response to EBV infection.

Two full spectrum flow panels have been validated for this purpose. A 24-colour panel has been designed to probe the wider circulating immune landscape of the study cohort (table 1). This is complemented by a targeted 30-colour T-lymphocyte panel that will elucidate any temporal changes in the T-lymphocyte compartment after transplantation (table 2).

**Table 1 T1:** Cell surface markers of interest used in the broad immune full spectrum flow for the Immunology of THymectomy And Childhood CArdiac transplant study

Cell surface marker	Fluorophore	Antibody clone	Purpose
CD45	Spark YG 593	HI03	Leucocytes
TCRγd	PerCP-eFluor 710	B1.1	γd T-lymphocyte
CD3	BV 510	SK7	Pan T-cell, NK T-like cells
CD4	PerCP	SK3	CD4 T-helper lymphocytes
CD8	BUV 805	SK1	CD8 cytotoxic T-lymphocytes
CD11c	PE-Cy7	B-ly6	Dendritic cell differentiation
CD14	Spark Blue 550	63D3	Monocyte differentiation
CD16	BUV 496	3G8	Monocyte, NK cell and dendritic cell differentiation
CD19	Spark NIR 685	HIB19	B lymphocytes
CD20	BV 786	2H7	B lymphocytes
CD21	PE-Cy5	B-ly4	B lymphocyte differentiation
CD24	PE-AF 610	SN3	B lymphocyte differentiation
CD27	APC-H7	M-T271	T/B lymphocyte differentiation

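### As most naturally read, the plan compares early thymectomy with late-thymectomy heart recipients and renal recipients pooled together, which mixes thymectomy timing with transplanted organ

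*Protocol article*

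**What the plan says.** The abstract of the protocol article describes 34 heart and 6 renal recipients "stratified into early (<1 year), late (>1 year) and non-thymectomy groups". Study design and setting identifies the third stratum as "a non-thymectomy age-matched control group made up of 6 renal transplant recipients".

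The Statistical analysis section then works with two sides rather than three. The linear and generalised linear mixed models are to find "Statistically different immune signatures between patients with early thymectomy and late or non-thymectomy", with "statistical significance defined as p<0.05". For the tetramer data, "Tetrameric frequencies for population groups (eg, early vs late/non-thymectomy) will be compared using Mann-Whitney U test". Tetramer counts are how EBV-specific T-lymphocytes are quantified, and their detection is one of the primary outcomes.

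The Introduction gives two statements about organ. It cites studies that found "marked phenotypic and functional disruptions to the T-lymphocyte compartment in paediatric heart transplant patients compared with children receiving a liver or kidney transplant". On PTLD it says: "Their incidence is allograft-dependent and ranges from 1%–2% in renal transplant recipients to as high as 10%–15% in heart transplant patients".

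The immunophenotyping section adds a further source of controls: "biobanked MNC samples from age-matched healthy children will be included for analysis as non-thymectomy, non-transplant controls".

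**The concern.** The study aims to identify the impact of early thymectomy. For that, the comparator should differ from the early group in thymectomy timing and as little else as possible. Late-thymectomy heart recipients share the organ with the early group; renal recipients do not. If the two are merged, any heart–kidney difference in the measured cells enters one side of the contrast only. The Mann-Whitney test takes no covariates, so nothing in that analysis can remove it.

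A significant early-versus-rest result could then arise with no effect of thymectomy timing, or a real effect could be offset and missed. Either way, the reader of the results could not tell which had happened. The same holds for the mixed models if they use a two-level group variable.

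**Working it through.** The article gives no power calculation, effect size or early/late split, so there is no figure of its own to reproduce for this contrast. The check has two parts.

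**Inputs from the article:** 34 hearts, 6 renal recipients, significance level 0.05.

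**Assumptions:** every heart recipient falls in the early or the late group; splits of 10/24, 17/17 and 24/10 (early/late); two-sided testing; normal data with SD 1; one time point; complete tetramer data; an organ difference (renal minus late heart) of 1 or 2 SD upward, and 1 SD downward.

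**1. Renal share and bias.** Renal share = 6 / (late hearts + 6). Expected pooled mean difference = thymectomy effect + renal share × organ difference.

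- 24 late: 6/30 = 20%, so 1 SD of organ difference shifts the contrast by 0.20 SD.
- 17 late: 6/23 = 26%, shift 0.26 SD.
- 10 late: 6/16 = 37.5%, shift 0.375 SD.

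**2. Rejection rates of the Mann-Whitney test** (20,000 simulated trials per setting).

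No thymectomy effect:

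| Early/late hearts | Pooled, no organ difference | Pooled, 1 SD | Pooled, 2 SD | Hearts only |
|---|---|---|---|---|
| 10/24 | 4.4% | 6.3% | 9.0% | 4.4–4.6% |
| 17/17 | 4.8% | 9.3% | 17.5% | 4.7–5.0% |
| 24/10 | 4.7% | 15.6% | 35.8% | 4.4–4.8% |

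True thymectomy effect of 0.8 SD (early group lower):

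| Early/late hearts | Pooled, renal 1 SD higher | Pooled, renal 1 SD lower | Hearts only |
|---|---|---|---|
| 10/24 | 69% | 31% | about 50% |
| 17/17 | 85% | 33% | about 59% |
| 24/10 | 91% | 20% | about 50% |

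At 17/17 the expected pooled difference is 0.8 + 0.26 = 1.06 SD in the first case and 0.8 − 0.26 = 0.54 SD in the second. The distortion therefore goes either way, depending on the sign of the organ difference.

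**Price of leaving the renal children out of the main contrast.** Ratio of standard errors = √[(1/early + 1/late) / (1/early + 1/(late + 6))]. At 17/17 this is √[(1/17 + 1/17) / (1/17 + 1/23)] = √1.15 = 1.07.

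**The case against.** The strongest reply is that pooling is inferred. The tetramer comparison is introduced as an example, and the slash could stand for two tests: early versus late, and early versus non-thymectomy. Mann-Whitney also suits pairwise comparisons among three groups, and a mixed model can carry a three-level factor. An analysis plan that is not shown may say so. This stands in part, because the wording does leave room. But late and non-thymectomy are put together in both sentences, against a single early group, and nothing in the article separates them. Pooling is the natural reading, and if separate contrasts are meant the text should say it.

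A second reply is that the heart–kidney gap may itself be partly a thymectomy effect, since the abstract proposes thymectomy as a reason for the disparity between heart and other recipients. Also, the PTLD incidence figures are not T-cell measurements. Both points are fair. They mean that the size of a separate organ effect is unknown, not that it is nil, and a pooled comparator cannot tell the two apart.

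A third is that the study is largely descriptive and the renal group is a deliberate design feature. Having the group is reasonable; the difficulty lies in merging it. The plan also attaches a significance threshold to the comparison.

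Three stronger readings are tempting but not supported:

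- **Healthy children are in the pool.** They share the non-thymectomy label, but the analysis sentence speaks of patients, the strata are defined within the 40 recipients, and the healthy samples are separately described as non-transplant controls. Nothing says they enter this contrast.
- **Immunosuppression differs between the two sides.** The article says only that therapy follows local protocols and gives no regimen by organ. A difference is plausible but inferred, and transplant-related immunosuppression could not affect pretransplant samples.
- **A heart-only contrast would isolate thymectomy.** The Introduction reports lower T-lymphocyte counts in congenital heart disease than in cardiomyopathy (CD4+ 430 against 963 cells/μL; CD8+ 367 against 765 cells/μL) and ties thymectomy to early cardiac surgery. Diagnosis may therefore still be confounded with timing.

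**Conclusion.** The point holds on the natural reading of the Statistical analysis section. Comparing early thymectomy with late and non-thymectomy children together confounds timing with organ, because all transplanted non-thymectomy children are renal recipients and the article's own background says heart and kidney recipients differ in the compartment being measured.

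The structure of the problem does not depend on the simulation; its size does. The range of about 6% to 36% false rejection covers the three assumed splits and organ differences of 1 to 2 SD. No single value in it should be read as the study's error rate: at 10/24 with 1 SD the inflation is slight, while at 24/10 with 2 SD it is severe. Actual tetramer numbers may also be smaller, since the tetramers are HLA-restricted and used only where applicable. The bias may inflate or mask the effect, and its direction is not known in advance.

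**What to change.** Revise the Statistical analysis section as follows:

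- Name early versus late thymectomy within heart recipients as the main thymectomy contrast.
- In the mixed models, use a three-level factor (early heart, late heart, renal) with separately reported contrasts.
- For tetramer frequencies, run separate pairwise Mann-Whitney tests, with renal recipients as their own reference group and not merged with late-thymectomy hearts.
- State that the healthy biobank children are a further separate reference and are not merged with any transplanted group.
- Adjust for underlying cardiac diagnosis in the models, or display results by diagnosis, and do not claim that the heart-only contrast isolates thymectomy.

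No change to recruitment or sampling is needed. The cost is the rewording and some precision, since the main contrast no longer uses the six renal children: about a 7% larger standard error at 17/17. By the same formula it is about 3% at 10/24 (√[(1/10 + 1/24) / (1/10 + 1/30)] = 1.03) and about 17% at 24/10 (√[(1/24 + 1/10) / (1/24 + 1/16)] = 1.17).

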#### Assessment and procedures

Children will undergo blood sampling for study-specific investigations during routine clinical visits prior to transplant and at 3, 6, 12 and 24 months post-transplant (figure 1). No additional study-related hospital visits are planned. Medical therapy will be applied as clinically indicated and per the local post-transplantation protocols. A total of 5–20 mL of blood will be taken at each study time point for all participants. This will coincide with their usual transplant-related investigations in adherence to WHO guidance for blood sampling in child health research.^15^ In the case of a prolonged interval between the pretransplant blood sample and subsequent organ transplant (eg, >6 months) additional blood samples will be specifically requested from the patient/parent and verbal consent recorded in the medical record. Relevant clinical data will also be collected from participants at each study time point (online supplemental table 1).

10.1136/bmjopen-2023-079582.supp1Supplementary data

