### Outcome measures

Primary outcomes measures:

Proportions of circulating innate and adaptive immune cell subsets before and at 3, 6, 12 and 24 months post-transplant.Frequency of detectable EBV-specific T-lymphocyte immunity.Functional capacity of EBV-specific T-lymphocytes.

Secondary outcome measures:

Incidence of EBV infection.Time from transplantation to EBV viraemia.Time from EBV viraemia to seroconversion.

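### Tetramer frequencies, which measure a primary outcome, are compared over time only in children with both samples and between groups separately, so no named tetramer test addresses thymectomy group by time

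*Protocol article*

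**What the plan says.** The Outcome measures section of the protocol article lists "Frequency of detectable EBV-specific T-lymphocyte immunity" among the primary outcomes, and tetramer staining is the assay that quantifies it. Samples "will be taken before transplant and at 3, 6, 12 and 24 months post-transplant", which makes five time points.

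The Statistical analysis section treats two kinds of data differently:

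- **Immune signatures.** Differences by thymectomy group, by EBV serostatus "and between time points, will be identified by linear and generalised linear mixed models", with "statistical significance defined as p<0.05".
- **Tetramer frequencies.** Groups (early versus late or no thymectomy) "will be compared using Mann-Whitney U test". Change over time is assessed "between time points for paired patient sample using Wilcoxon signed-rank test".

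The Sample size calculation section accepts that some listed children will not be transplanted while the study runs. It says that "any pretransplant blood samples that have been obtained are equally important" for the primary outcome measure. It also calls the objectives largely descriptive.

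The article does not say which pairs of time points will be compared, and it mentions no multiplicity correction for these tests.

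**The concern.** A signed-rank test uses only children who have both samples of the pair. A child sampled once contributes to no comparison over time, and the article plans for such children. The children who contribute also differ from pair to pair, so the contrasts do not describe one trajectory in one set of patients. In the standard form of the test zero differences are dropped as well, so a child with no detectable tetramer-positive cells at both visits adds nothing.

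The larger matter is the question being answered. The stated aim is the effect of early thymectomy on the immune response to EBV over time, which is a group-by-time question. As described, the Mann-Whitney test compares groups without time and the signed-rank test compares times without group. Neither adjusts for EBV status or age. A study that follows children for two years to see whether trajectories diverge would then have no estimate of that divergence for this primary outcome.

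**Working it through.** The article gives no error rate, precision or missing-data rate for this analysis, so there is no stated figure to reproduce.

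**Inputs from the article:** 34 heart recipients, 6 renal controls, five time points, significance at p<0.05 (stated for the mixed models; taken here as two-sided and as applying to the rank tests too).

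**Assumptions:** each sample is available with probability *a* = 0.9, 0.8 or 0.7, independently and completely at random; within-child correlation ρ = 0.5, equal between all visits; unit variance.

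**Step 1: pairs per comparison.** Expected complete pairs = n × a².

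| a | n = 34 | n = 40 |
|---|---|---|
| 0.9 | 34 × 0.81 = 27.5 | 32.4 |
| 0.8 | 34 × 0.64 = 21.8 | 25.6 |
| 0.7 | 34 × 0.49 = 16.7 | 19.6 |

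Tetramers are used only where they match the child's HLA type, so the true counts will be lower.

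**Step 2: what this costs in precision.** For pre-transplant versus 3 months, the complete-pairs variance of the mean difference is 2(1 − ρ)/pairs, which is 1/pairs at ρ = 0.5. The all-samples variance comes from generalised least squares: add the inverse covariance matrices of each child's observed visits, invert the sum, and read off the contrast. Both were averaged over simulated missing-data patterns with n = 34. This compares means rather than ranks, as a guide to the information each approach keeps.

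| a | complete pairs vs no missing data, √(34/pairs) | complete pairs vs all samples | all samples vs no missing data (column 2 / column 3) |
|---|---|---|---|
| 0.9 | 1.11 | about 1.04 | 1.07 |
| 0.8 | 1.25 | about 1.09 | 1.15 |
| 0.7 | 1.43 | about 1.16 | 1.23 |

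Column 3 moves by about 0.01 with the way the runs are averaged. If six of the 34 children have a pre-transplant sample only, the penalty in column 3 becomes about 7% to 21%. Most of the loss from missing visits therefore falls on either method. The part that a mixed model recovers is column 3.

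**Step 3: number of tests.** Five time points give 5 × 4 / 2 = 10 possible pairs per tetramer readout. At 0.05 each, 1 − 0.95¹⁰ = 40.1% if the tests were independent. Simulation with ρ = 0.5 and no true change gives about 28% to 35%. If only the four comparisons with pre-transplant are meant, the figures are 1 − 0.95⁴ = 18.5% and about 14% to 17%. Lytic and latent tetramers tested separately over all pairs would make 20 tests (64% if independent).

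**Step 4: which mixed model.** A binomial or Poisson model with a child random effect alone treats ordinary visit-to-visit variation as evidence of change. In simulation with no true change and visit-level log-SD of 0.2 to 0.5 (assumed), its overall time test rejected 27% to 98% of the time. The rate depends on the assumed cell counts and spread. A linear mixed model on log frequency stayed close to 5%.

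**The case against.** The case for leaving the plan alone has several sound parts.

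- **Rank tests are defensible here.** Tetramer frequencies are rare, skewed and perhaps full of zeros, and the cohort is small. A careless count model would be worse, as step 4 shows. This stands, and it governs the form of the fix.
- **Ten uncorrected tests.** A reader might infer that all ten pairs will be tested without correction. The article does not say so: ten is the maximum, four comparisons with baseline fit the text equally well, and silence on correction in a condensed article is not a decision against it. Nor does the signed-rank test cause multiplicity, because ten contrasts from a mixed model would raise the same issue. The descriptive aim lessens this part further.
- **Precision.** A reader might infer from the fall in pairs from 34 to about 17 that precision collapses. It does not, because the mixed model also suffers most of that loss.
- **Children sampled only before transplant.** They are not lost to the study. They can enter the mixed models for cell subsets and the Mann-Whitney group comparison at baseline, and no method observes change within a child sampled once. Their samples would still inform the baseline mean in a mixed model.
- **Bias from sicker children missing visits.** This is possible, but the documents give no figure, and a mixed model also needs missingness to be explained by what was observed.
- **Tetramers may already be in the mixed models.** Tetramer channels belong to the T-lymphocyte panel, and nothing excludes them from the immune signatures. The article does not say they are included, however. The only methods it names for tetramer frequencies are the two rank tests.

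**Conclusion.** The point holds as a modest but worthwhile correction. The article commits to a paired-only test for change over time in a primary-outcome assay, while it expects incomplete series and names a method in the same section that would use them. The gap in substance is that no method named for tetramer frequencies estimates thymectomy group by time. That gap does not depend on any assumed figure.

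The efficiency cost is small to moderate: about 4% to 16% in standard error for availability of 90% to 70%, or about 7% to 21% if six children have only a pre-transplant sample. Both ranges rest on n = 34, correlation 0.5 and data missing completely at random, before any loss from HLA coverage. On multiplicity, the documents support only that the pairs to be tested are unspecified and that no correction is mentioned.

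**What to change.** Make the mixed model already named in the Statistical analysis section the main analysis of tetramer frequency:

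1. Child as random effect, time as a five-level factor, thymectomy group, and thymectomy group by time.
2. Either log-transformed frequency in a linear mixed model, or a generalised model for the counts that allows visit-to-visit overdispersion (an observation-level random effect or a beta-binomial). Do not use a binomial model with a child effect alone.
3. Report one overall test of time and one of group by time. Follow with four contrasts against pre-transplant, adjusted for multiplicity (Bonferroni would be 0.05/4 = 0.0125 each).
4. Keep the signed-rank and Mann-Whitney tests as sensitivity analyses, and state which time pairs they cover.

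If tetramer frequencies were always meant to enter the mixed models, it is enough to say so and give the model's form.

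The cost is a change of wording and some extra modelling, with no new samples, visits or patients. The downside is a distributional assumption for rare and possibly zero-heavy frequencies, including how zeros are handled before taking logs. The rank tests serve as the check on it.
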